## Methods/design

### Objectives

The primary objective of this study is to compare the accuracy of achieving the planned centre of hip rotation in CO THA versus RO THA. This will be assessed within each treatment group by measuring the difference in the achieved centre of rotation on postoperative CT scanogram compared to the planned centre of rotation on preoperative pelvic CT scan. The study hypothesis is that RO THA will improve the accuracy of achieving the planned centre of rotation compared to CO THA.

The secondary objectives are to compare the following outcomes between the two treatment groups:
Accuracy of achieving planned component positioningAccuracy of restoring planned hip biomechanicsSpinopelvic functional kinematicsSurgical efficiencyPostoperative functional rehabilitationFunctional outcomesQuality of lifeRange of motionResource use and cost-effectivenessComplications

Specific study outcomes related to the primary and secondary objectives are discussed in the “Outcomes” section below.

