### Sample size

Prior to commencement of this study, a pilot study was performed to assess the accuracy of restoring the centre of rotation using CO THA versus RO THA [15]. Using data from this study, the mean centre of rotation was set at 3.7 mm for CO THA and 2.9 mm for RO THA, with standard deviation of 1.0 mm. Using a two-tailed, two sample *t* test with a power of 80% (1–*β*), significance level of 5%, and an effect size of 0.8, this study required 52 patients (26 in each treatment arm) to detect the minimum difference between the two treatment groups. To account for 10% attrition in the sample size during follow-up, the total sample size was set at 60 patients.

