### Statistical analysis

The analysis of the per-protocol population will be considered the primary analysis. The differences between the CO THA and RO THA groups will be analysed by calculating the difference from baseline, per patient, and a two-sided confidence interval for the difference between the changes from baseline values will be calculated. This confidence interval will cover the true difference in the percentage change from baseline with a probability of 95%. The following statistical methods will be employed to analyse the data: descriptive statistics, independent *t* test, paired *t* test, analysis of variance, Fisher exact test, chi-square test, and graphical displays. Assumptions of normality will be tested with the D’Agostino test. Assumptions of homogeneity of variance will be tested with Levene’s test. If the distributional assumptions are (severely) violated, non-parametric techniques, such as Mann-Whitney’s test will be employed. In the event that RO THA is converted to CO THA intraoperatively, analysis will be performed using the intention-to-treat population and the treatment actually received by the patients. Intraoperative conversion from RO THA to CO THA will be documented and presented and published as part of the study. All statistical analysis will be undertaken by a blinded observer. Statistical significance is set at a *p* value < 0.05 for all analyses, and all statistical analysis will be performed using SPSS software version 25 (SPSS Inc., Chicago, IL, USA).

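### One confidence interval is given two different targets (change and percentage change from baseline), and change from baseline does not fit the deviation-from-plan primary endpoint that was powered

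*Protocol article*

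**What the plan says.** All references are to the protocol article.

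- **Objectives.** The primary endpoint is obtained by "measuring the difference in the achieved centre of rotation on postoperative CT scanogram compared to the planned centre of rotation" on the preoperative CT. The hypothesis is that "RO THA will improve the accuracy of achieving the planned centre of rotation compared to CO THA".
- **Outcomes.** The CT scanogram is done once, 6 weeks after surgery. Horizontal and vertical centres of rotation are listed as separate items. Hip scores and EQ-5D are recorded before and after surgery. Operating time and time to discharge have no preoperative value.
- **Sample size.** From pilot data, "the mean centre of rotation was set at 3.7 mm for CO THA and 2.9 mm for RO THA", "with standard deviation of 1.0 mm". The test is a two-sided two-sample t test with effect size 0.8, 80% power and 5% significance, giving 26 per arm, and 60 in total after allowing for attrition. No baseline and no percentage enters this calculation.
- **Statistical analysis.** The arms are to be compared by "calculating the difference from baseline, per patient, and a two-sided confidence interval for the difference between the changes from baseline values will be calculated". The next sentence describes the same interval: "This confidence interval will cover the true difference in the percentage change from baseline with a probability of 95" per cent. A list of tests follows (t tests, analysis of variance, Fisher exact, chi-square, Mann-Whitney as fallback), none of them assigned to a named outcome.

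**The concern.** There are two defects in the text as it stands, and one ambiguity that follows from the second.

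1. The interval is constructed for one parameter and claimed to cover another. Whichever was meant, one of the two adjacent sentences is wrong.
2. The only between-group effect that the section describes needs a baseline. Deviation from plan does not exist before surgery, so the description does not reach the primary endpoint, and it is not the quantity on which the trial was sized.
3. A reader who tries to apply the sentence to the primary endpoint will probably treat the planned position as the baseline. A change is ordinarily signed. A mean of signed deviations measures average bias, whereas the hypothesis is about accuracy.

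At stake is the definition of the primary result. With the text as written, the metric could be settled after the data are seen, and the published interval could carry a description that does not match its construction.

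**Working it through.** **Step 1. The planned sample size.** Inputs from Sample size: difference 3.7 − 2.9 = 0.8 mm, SD 1.0 mm, so d = 0.8/1.0 = 0.8; two-sided 5%; power 80%. The noncentral t calculation gives 25.52, so 26 per arm, 52 in total, with power 80.7% (86.1% at 30 per arm). For 10% attrition, 52/0.9 = 57.8, so 58; the plan takes 60. The plan's figure reproduces. It rests on a plain comparison of mean deviations in mm.

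**Step 2. The two targets of the interval.** Write B for a patient's baseline and Y for the later value.

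- Change: Y − B, in the units of the outcome.
- Percentage change: 100 × (Y − B)/B, without units.

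The second divides each patient's change by that patient's own B. The between-arm difference in one is therefore not the between-arm difference in the other, even after rescaling, unless all patients share the same B. An interval for the first has no claim to 95% coverage of the second. For the primary endpoint the percentage has a further problem: if B is a planned coordinate, its value depends on where the origin is placed.

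**Step 3. Stated analysis against powered analysis.**

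| | Sample size | Statistical analysis |
|---|---|---|
| Per-patient quantity | deviation, positive means in mm | change from baseline |
| Baseline needed | no | yes |
| Scale of effect | mm | change, then percentage change |

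**Step 4. What the signed reading would do.** This step is conditional on taking the plan as baseline and keeping the sign. Magnitudes are those in Sample size (means m = 3.7 and 2.9 mm, SD 1.0). The share q of errors in one direction is not in the documents; it is an assumption, varied here and kept equal in both arms. For each arm:

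- signed mean = m(2q − 1)
- signed SD = √(1.0² + m² − [m(2q − 1)]²)

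Example at q = 0.8: the difference in means is 0.8 × 0.6 = 0.48 mm. The variances are 1 + 13.69 − 13.69 × 0.36 = 9.76 and 1 + 8.41 − 8.41 × 0.36 = 6.38. The standard error at 26 per arm is √[(9.76 + 6.38)/26] = 0.79 mm, so the difference is only 0.48/0.79 = 0.61 standard errors. For absolute deviation it is 0.8/√(2/26) = 0.8/0.277 = 2.9 standard errors.

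Simulated power of the two-sample t test, 26 per arm:

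| Direction split | Difference in signed means (mm) | Signed SD, CO / RO (mm) | Power, signed | Power, absolute |
|---|---|---|---|---|
| 50/50 | 0.00 | 3.83 / 3.07 | 5% | 81% |
| 70/30 | 0.32 | 3.54 / 2.84 | 7% | 81% |
| 80/20 | 0.48 | 3.12 / 2.53 | 10.5% | 81% |
| 90/10 | 0.64 | 2.43 / 2.01 | 21% | 81% |
| all one way | 0.80 | 1.00 / 1.00 | 81% | 81% |

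Only the last row restores the planned power.

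**The case against.** The strongest reply is that the planned position on the preoperative CT is a natural reference. Taken as the baseline, and with the difference read as a magnitude, the per-patient quantity is the deviation from plan. The independent t test that the section lists is then exactly the powered test. The endpoint is called accuracy, and the positive means of 3.7 and 2.9 mm point to magnitudes. No sentence says that the sign is kept. If the powered metric is a combined distance, it is unsigned by construction and cannot cancel.

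Much of this stands. A reader might infer that the protocol prescribes a signed analysis, or that the primary test has no power. The documents support neither: sign against magnitude is left open, and 5% is one end of a range that depends on a directional split the documents do not give.

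It is also fair that change from baseline suits the hip scores and EQ-5D, and that the listed tests can serve complications, operating time and time to discharge. The section does not say that change from baseline is the only analysis.

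What the reply does not meet is the coverage sentence. No reading makes one interval serve both targets, and the percentage form has no sensible meaning for a deviation from plan. Nor can the point be put down to an article condensing a fuller document: an analysis and a coverage property are stated here, and the property is wrong.

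**Conclusion.** The point holds in two parts, both on the text alone. The sentence attributing 95% coverage of the percentage change to an interval for the change is wrong. And change from baseline, given without limitation as the between-group analysis, does not fit the primary endpoint, which has no preoperative value and was powered as a two-sample comparison of mean deviations in mm.

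The loss of power is conditional. It needs the plan to be treated as baseline and the sign to be kept, and its size rests on assumed direction splits: about 5% to 81% at 26 per arm on the protocol's own magnitudes, against about 81% for absolute deviation. It shows why the ambiguity should be closed; it is not a forecast for this trial. The sample size is not in error.

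**What to change.** 1. Delete the percentage-change sentence, or correct it so that the interval is described by the quantity it is built for.
2. State the primary effect: the between-arm difference in mean absolute deviation of achieved from planned centre of rotation, in mm, at 6 weeks, with its 95% confidence interval from the two-sample t procedure.
3. Name the metric (horizontal, vertical or combined) and use the one that gave 3.7 and 2.9 mm in the pilot data. A combined distance should not be imposed by default: Outcomes lists the two components separately, and Sample size does not say which quantity was powered.
4. Limit change-from-baseline analyses to outcomes with a preoperative value, such as the hip scores and EQ-5D.

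The cost is a change of wording, plus a look at the pilot data to confirm the metric. No new data are needed. On the powered metric the sample size stays at 52 evaluable patients, 60 with attrition. The change should be made and dated before the arms are compared.

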Evolution in surgical technology has led to the development of robotic-arm assisted THA (RO THA), which aims to facilitate preoperative surgical planning, reduce intraoperative errors in bone resection, and improve the accuracy of implant positioning compared to CO THA. Preoperative computerised tomography (CT) scans of the pelvis and proximal femur are used to create virtual three-dimensional reconstructions of the patient’s anatomy. The surgeon uses this patient-specific computer-aided design (CAD) model to map optimal implant positioning to achieve the desired bone coverage, component positioning, hip biomechanics, and correction of any limb-length discrepancy. An intraoperative robotic device with audio, visual, and tactile feedback helps to execute the planned bone resection and implant positioning plan with a high level of accuracy. Existing reports comparing CO THA versus RO THA have shown conflicting outcomes [6, 14, 15, 20, 22]. Initial studies found RO THA was associated with improved functional outcomes as assessed using the Harris ship score, increased accuracy of acetabular implant positioning, better preservation of acetabular bone stock, improved restoration of native femoral offset, and reduced postoperative leg-length inequality compared to CO THA [6, 7, 9, 14, 15, 20]. However, further studies have shown no difference in CO THA versus RO THA with respect to functional outcomes, implant survivorship, and complications at short-term follow-up [4, 17, 19, 21]. Delays in the widespread implementation of RO THA have been attributed to the limited data showing any functional benefit with this procedure compared to an already established and highly cost-effective CO THA [7, 13].

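### If its assumption tests fail, the plan moves to Mann-Whitney, which neither corrects for unequal variances nor tests the mean difference the trial is sized on; a pre-specified Welch test would do both

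*Protocol article*

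**What the plan says.** Four consecutive steps in the protocol article's Statistical analysis section matter here.

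- The independent t test heads the list of methods for comparing the arms.
- "Assumptions of normality will be tested with the D’Agostino test", and "Assumptions of homogeneity of variance will be tested with Levene’s test".
- The next sentence gives the consequence: "If the distributional assumptions are (severely) violated, non-parametric techniques, such as" Mann-Whitney's test are to be used.
- The threshold is common to everything: "Statistical significance is set at a *p* value < 0.05 for all analyses".

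The same section also promises, without conditions, that "a two-sided confidence interval for the difference between the changes from baseline values will be calculated".

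The Sample size section works with means of 3.7 mm (conventional) and 2.9 mm (robotic), one SD of 1.0 mm, and a two-sided two-sample t test.

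**The concern.** The rule treats a rank test as the remedy for a failed variance test. Mann-Whitney is not one. Its null distribution assumes that the two arms have the same distribution, and what it measures is the probability that a patient in one arm has a larger error than a patient in the other. When spread and skew differ between arms, that probability can differ from one half although the means are equal. It can also sit closer to one half than the difference in means would suggest.

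Two things are at stake. First, the test that decides the primary question could address a different quantity from the one powered and from the one in the confidence interval, so the two could point different ways. Second, the choice would depend on the data, through tests that may well be triggered here. Unequal spread is plausible because the Background describes a device meant to "execute the planned bone resection and implant positioning plan with a high level of accuracy", and a distance from plan cannot be negative, so it is often skewed.

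**Working it through.** **1. The plan's own figure.** Normal approximation: n per arm = 2(1.960 + 0.842)² × 1.0² / 0.8² = 2 × 7.85 / 0.64 = 24.5, so 25. The noncentral t gives 26 per arm (52 in total) with 80.7% power, as stated. Allowing for attrition, 52 / 0.9 = 57.8, so 58; the plan rounds up to 60. The sizing is for a difference in means with one common SD. After 10% loss, 60 × 0.9 = 54, or 27 per arm.

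**2. Assumptions that the document does not supply.**
- Ratio r of conventional to robotic SD: 1.5 to 3.
- Error shape: normal, gamma or lognormal.
- Trigger: Mann-Whitney if Levene or D'Agostino gives p<0.05, otherwise the pooled t test.
- The protocol's 1.0 mm is kept as the pooled SD: SD(robotic) = √(2/(1 + r²)) and SD(conventional) = r × SD(robotic). For r = 2 these are 0.632 and 1.265 mm; for r = 3, 0.447 and 1.342 mm.

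**3. How often the switch would occur.** With normal errors and 26 per arm, Levene rejects in 45%, 87% and 99.7% of simulated trials at r = 1.5, 2 and 3.

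**4. Why equal means can still be rejected.** Take lognormal errors, r = 3, both means 3.3 mm. The log-scale variances are ln(1 + 1.8/10.89) = 0.153 and ln(1 + 0.2/10.89) = 0.018. The log-scale means differ by (0.153 − 0.018)/2 = 0.067. Then P(conventional error < robotic error) = Φ(0.067/√0.171) = Φ(0.16) = 0.56. The rank test sees a difference, here against the robot, where the means have none.

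**5. Type I error of the two-stage rule** (equal means of 3.3 mm, pooled SD 1.0 mm, 27 per arm, 8,000 simulated trials):

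| SD ratio | normal | gamma | lognormal |
|---|---|---|---|
| 1.5 | 5.3% | 5.9% | 7.0% |
| 2 | 5.6% | 7.7% | 9.6% |
| 3 | 5.9% | 10.7% | 14.1% |

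Repeat runs move these by up to about one percentage point.

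**6. If conventional spread is larger than planned.** Fix the robotic SD at 1.0 and raise the conventional SD to 2 or 3 mm. The lognormal figures become about 14% and 34%. The pooled SD is then √(5/2) = 1.58 or √(10/2) = 2.24 mm, well above the protocol's 1.0. On the same settings with 26 or 30 per arm, Welch has 4.7–5.9% up to ratio 2 and 6.5–8.2% at ratio 3 with skewed errors.

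**7. Power at the design difference** (3.7 v 2.9 mm, r = 2, 26 per arm). Normal errors: two-stage rule 77.7%, Welch 80.8%. Gamma errors: 72.1% and 81.9%. Over the three shapes and repeat runs the ranges are about 71–78% and 80–84%.

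**8. A case with no false positives.** If the robot only shrinks a two-axis distance error (Rayleigh distribution), equal means imply identical distributions and Mann-Whitney holds 4.8%. The cost is then power: at a scale ratio of 1.5, 68% for Mann-Whitney against 76% for the t test.

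**The case against.** **The rule is softer than the simulated one.** The word *severely* has no cut-off and the fallback is only given as an example, so an automatic switch at p<0.05 is an assumption. The cut-off may be fixed in an analysis plan that is not shown, and its absence from an article is no fault. One could also read the fallback as concerning normality alone, with Levene's test choosing the form of the t test. The order of the sentences favours the wider reading but does not prove it. All this stands, and it makes the rates in the working conditional. It does not change the fact that the only remedy named is a rank test.

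**Unequal spread is not stated.** A reader might infer that a more accurate robot must produce unequal variances. The document does not say so, and its sample size uses one SD. The arm-specific spreads in the Background are mixed: in the retrospective CT comparison the SDs are 23.6 v 11.7 (ratio 2.0) for combined anteversion but 6.8 v 6.0 (ratio 1.1) for cup inclination, and neither is the primary outcome.

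**The null may be artificial.** For a distance error, less spread usually means a smaller mean, and then there is no false positive to count. This stands; in that case the harm is to power and interpretation.

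**The interval is not withdrawn.** A reader might infer that the confidence interval is dropped after a switch. The sentence promising it is unconditional, so the risk is disagreement between interval and p value, not loss of the interval.

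**The analyst is blinded.** That limits choosing a test for its result, though the choice still depends on the data.

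**Conclusion.** The concern holds as a mismatch of method. The published fallback is no remedy for unequal variances and does not test the mean difference that the trial is sized on. This needs no simulation.

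The numerical harm rests on three assumptions: unequal spread, the shape of the errors, and a p<0.05 trigger. With equal arms and near-normal errors it is small (5–7%). With skewed errors at the protocol's pooled SD it is moderate: about 7–10% at ratio 2 and 10–14% at ratio 3. Under the trial's own hypothesis at ratio 2, the cost is roughly 3 to 10 points of power in a trial planned with about 80%.

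A reader might infer that the plan simply fails to keep its 5% level, or take 34% as the expected error. The documents support neither. Mann-Whitney keeps 5% for its own null of identical distributions, and the 34% needs a threefold SD ratio, lognormal skew and a pooled SD more than twice the protocol's.

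**What to change.** Replace the pre-test rule with one sentence: the primary analysis is Welch's unequal-variance t test, with its 95% confidence interval for the difference in mean error (mm), whatever the normality and variance tests show. Add a bootstrap interval as the sensitivity analysis for skewness, and label any rank test as supportive. Test, estimate and sample size then refer to the same quantity.

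The cost is small but not nil:
- If variances are equal, the power loss is negligible (normal errors at the design difference: 80.4% for Welch, 80.5% for the pooled t test).
- If errors are skewed with equal spread, a rank test would have been somewhat stronger (gamma errors: 81.6% against 80.3%), more so with heavier skew.
- In the most extreme skewed cases Welch itself reaches about 6–8% type I error, which is why the bootstrap interval belongs beside it.

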### Adverse events

Adverse events are defined as any untoward medical occurrence in a patient or study participant, which does not necessarily have a causal relationship with the procedure involved. A serious adverse event (SAE) is an adverse event that results in hospitalisation or prolongation of existing hospitalisation, persistent or significant disability or incapacity, life-threatening clinical sequelae, or death. All SAEs during the protocol treatment will be reported directly to the sponsor using the SAE web form. The chief investigator will also assess the SAE for severity, causality, seriousness, and expectedness using pre-existing criteria provided by the sponsor and inform the Data Safety Monitoring Board (DSMB) within 3 days of the initial observation of the event. The protocol treatment period is defined as the period from the day that the first study patient is recruited into the trial to the day that the final study patient has completed the 2-year follow-up. The chief investigator will also inform the London-Bromley Research Ethics Committee and local Health Research Authority within 3 days of the SAE taking place. Safety aspects of the study are closely monitored by the sponsor and DSMB using unblinded data for its judgement. In cases where the SAE arises due to a problem with the robotic device, Stryker Limited will also be notified within 2 days of the event taking place. The chief investigator will record the following: onset date, complete description of the event, severity, duration, action taken, and outcome for each SAE. The chief investigator will also provide regular updates of all SAEs to the London-Bromley Research Ethics Committee, local Health Research Authority, DSMB, and sponsor.

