### Trial design

This study is a prospective, single-centre, randomised controlled trial. The study will be undertaken in the Department of Trauma and Orthopaedics, University College Hospital, [name]. The study will include 60 patients randomly allocated to either CO THA (control group) or RO THA (investigation group). The study commenced patient recruitment in December 2018 and is expected to complete patient recruitment in December 2020. All patients will be followed up for 2 years after surgery, and therefore, the anticipated completion date for the study is December 2022. The study is sponsored by University College London, UK. The patient enrolment flow chart is presented in Fig. 1. The schedule of enrolment, interventions, and assessments for all study patients is shown in Fig. 2.

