### Outcomes

All study patients will undergo review by two observers (one orthopaedic registrar and one clinical research fellow) at 6 weeks, 6 months, 1 year, and 2 years following surgery. During these follow-up times, predefined clinical, functional, and radiological outcomes will be recorded by these observers using case report forms (CRFs). The following outcomes will be recorded in all study patients:
Accuracy of achieving the planned implant positioning and hip biomechanics (horizontal centre of rotation, vertical centre of rotation, acetabular offset, femoral offset, and leg-length discrepancy) as assessed using CT scanograms performed postoperatively at 6 weeksOperating time (minutes)Time to hospital discharge (hours)Analgesia requirements during inpatient admission and postoperatively at 6 weeks, 6 months, 1 year, and 2 yearsPatient-reported outcome measures including Oxford hip score (OHS), Harris hip score (HSS), Hip disability and osteoarthritis outcome score (HOOS), University College Hospital hip (UCH) score, Western Ontario and Mcmaster Universities Osteoarthritis Index (WOMAC), and University of California at Los Angeles hip (UCLA) score preoperatively and postoperatively at 6 weeks, 6 months, 1 year, and 2 years following surgeryHealth-related quality of life as measured using European Quality of Life questionnaire with 5 dimensions for adults (EQ-5D) preoperatively and postoperatively at 6 weeks, 6 months, 1 year, and 2 yearsMobilisation distance (metres) and use of mobility aids during inpatient admission and postoperatively at 6 weeks, 6 months, 1 year, and 2 yearsRange of movement (degrees) in the hip joint in the supine position as assessed with a goniometer during inpatient admission and postoperatively at 6 weeks, 6 months, 1 year, and 2 yearsResource use and cost-effectiveness including comparisons between the two treatment groups relating to operating time, theatre efficiency, equipment and sterilisation costs, analgesia requirements, inpatient rehabilitation, time to discharge, outpatient follow-up, additional imaging costs, and need for further surgeryComplications

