### End of protocol treatment

Reasons for going off study protocol include:
Completion of last follow-up visit 2 years after surgeryPatient non-compliance or withdrawal (the reason for discontinuation will be recorded in the case report form)Intercurrent death

All patients included into this study are free to withdraw from the study at any time without compromise to their future treatment. On withdrawal, patients will revert to the standard follow-up regimen for routine (non-study) THA at the study site. The end of study form will be completed and the reason for withdrawal documented. This form will also be completed if the patient is lost to follow-up or dies during the course of the study. Data to the point of discontinuation will be used for analysis.

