## Trial status

Protocol: version 3.0; date 26 October 2018

Patient recruitment date: 1 December 2018

Estimated completion of the recruitment date: 1 December 2020

Estimated completion of the final follow-up: 1 December 2022

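### The SAE reporting period is defined trial-wide, but patients leave the protocol one by one, including for non-compliance; the two rules need reconciling, and complications in early leavers may be lost informatively

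*Protocol article*

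**What the plan says.** The Adverse events section sets the reporting duty: "All SAEs during the protocol treatment will be reported directly to the sponsor using the SAE web form". It then defines the period. "The protocol treatment period is defined as the period from the day that the first study patient is recruited into the trial" gives the start, and "to the day that the final study patient has completed the 2-year follow-up" gives the end. Both are dates of the trial, not of the individual patient.

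The End of protocol treatment section uses the same term in its heading but lists exits for individual patients: the 2-year visit, non-compliance or withdrawal, and death. It adds "On withdrawal, patients will revert to the standard follow-up regimen for routine (non-study) THA at the study site" and "Data to the point of discontinuation will be used for analysis".

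Two other sections set a common follow-up. Trial design says "All patients will be followed up for 2 years after surgery". Outcomes schedules review "at 6 weeks, 6 months, 1 year, and 2 years following surgery. During these follow-up times, predefined clinical, functional, and radiological outcomes will be recorded", and complications are on its list. Complications are also a secondary objective.

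**The concern.** One term has two different ends, and the SAE duty hangs on that term. Site staff could not tell from these sections whether an admission 30 months after surgery is reportable, or whether one at month 10 is reportable in a patient who withdrew at month 6.

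The second case matters more for the analysis. Non-compliance is a listed reason for going off protocol, and the analysis uses data up to discontinuation. A patient with a dislocation, an infection or a revision may plausibly miss reviews or fall behind in the rehabilitation programme. If that counts as non-compliance, follow-up can end because of the very outcome being counted. The Blinding section says that patients cannot be blinded, so early exit could also differ between arms. With 60 patients, a few unrecorded events could change how the complication comparison looks.

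**Working it through.** **1. The two definitions side by side**

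| Patient | Adverse events section | End of protocol treatment section |
|---|---|---|
| Completes the 2-year visit early in the trial | SAEs reportable until the last patient's 2-year visit | Off protocol at own 2-year visit |
| Withdraws | SAEs reportable until the same trial-wide date | Off protocol; routine follow-up; data to discontinuation used |
| Non-compliant | As above | Off protocol; data to discontinuation used; routine follow-up not mentioned |

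The definitions disagree in every row. The second section does not mention SAEs, so an end to SAE collection could only be inferred from the shared term.

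**2. Length of the trial-wide window**

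Inputs: "Patient recruitment date: 1 December 2018"; the Trial status section also gives end of recruitment as 1 December 2020 and final follow-up as 1 December 2022. Consent is 2 weeks before surgery (Consent section). Even accrual of 60 patients is an assumption.

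- First patient: December 2018 to December 2022 = 4.0 years.
- Last patient: December 2020 to December 2022 = 2.0 years.
- Mean under even accrual: (4.0 + 2.0)/2 = 3.0 years; 60 × 3.0 = 180 patient-years.
- Scheduled follow-up from consent: 2 + 2/52 ≈ 2.04 years; 60 × 2.04 ≈ 122 patient-years.
- Share after the last scheduled visit: (180 − 122)/180 ≈ 32%. Counting from surgery instead, (180 − 120)/180 = 33%.
- Longest tail for one patient: 4.0 − 2.04 = 1.96 years.

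**3. Would the unequal window bias the arms?**

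Entry date is independent of randomised arm. Under even accrual the window has an SD of about 0.59 years. With 30 per arm, the standard error of the difference in mean window is 0.59 × √(2/30) ≈ 0.15 years, around an expected difference of zero. The unequal window blurs the denominator but favours neither arm.

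**4. How many patients the exit rule may touch**

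The Sample size section needs 52 patients and allows 10% attrition: 52/0.9 = 57.8, so 58, and the stated 60 covers it. Ten per cent of 60 is 6. This is an allowance for all causes, not a non-compliance rate, and no rate by arm is given.

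**5. How many events could be lost**

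The documents give no complication rate. If it were 5 to 10% (assumed), 60 patients would have 3 to 6 events. Six leavers at the same risk would have 6 × 0.05 = 0.3 to 6 × 0.10 = 0.6 events, including any before they left. A larger loss needs leavers to be at higher risk. That is the worry with informative exit, but the documents give nothing to quantify it.

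**The case against.** The strongest reply is that the sections can be read together. One sets the calendar period during which the trial reports SAEs to the sponsor and the DSMB; the other says how an individual leaves. A reader might infer that SAE collection stops at discontinuation, but no sentence says so. The return to routine follow-up is stated for withdrawal only, and it takes place at the study site, so such patients are not out of sight.

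A reader might also infer that complications are compared over unequal, partly unobserved follow-up of 2 to 4 years. The documents do not support that. Trial design and Outcomes give everyone the same 2 years, and nothing says that the comparison uses the SAE reporting window. Nor do they support a figure for the share of events lost, which would stack an assumed loss on an assumed event count.

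Finally, this is a condensed article, and the full protocol may define non-compliance and say how SAEs are handled after withdrawal. The lack of those details is therefore not the point.

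All of this stands, and it removes the calendar window as a source of bias. It does not remove two things that the article itself states: one term with two ends, and a rule that lists non-compliance as an exit and uses data to that point. The common 2-year schedule does not help there, because the truncation falls within the 2 years.

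**Conclusion.** The point holds in a limited form. The two sections define the same period incompatibly and must be reconciled. The 2-to-4-year window, about one third of it after the last scheduled visit if accrual is even, is an ambiguity about what is reportable and over what denominator. It is not a between-arm bias.

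The substantive weakness is taking non-compliant or withdrawn patients off protocol and using their data only to that point, which is the natural reading of the rule. This can lose complications informatively, and possibly unequally, because patients are unblinded. About 6 of 60 patients are at issue if the attrition allowance is right. The number of events lost, and any difference by arm, cannot be estimated from the documents. The sample size and the primary outcome, read on the 6-week CT, are not in question. This is a cheap improvement worth making, not a fatal flaw.

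**What to change.** - Reconcile the two sections so that the term for the SAE reporting period has one meaning.
- Delete non-compliance as a reason to end follow-up.
- When a patient stops attending visits, keep collecting SAEs, further surgery and death to 2 years after surgery from the medical notes, unless consent for data use is withdrawn. The Consent section already tells patients that the research team will review their notes.
- State that the between-arm comparison of complications covers each patient's 2 years after surgery. Leave safety reporting to the sponsor and DSMB over the trial-wide period as wide as it is now.

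The cost is a wording change in a few places and a short note review for a handful of patients, about six on the plan's own allowance. Events treated at other hospitals may still be missed. Events after a patient's second year would be reported as safety information but not counted in the comparison. Clinical care does not change.
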